### GM detection

Peripheral venous blood will be collected into Vacutainer® tubes (BD Worldwide, Suzhou, China), and serum will be obtained by centrifugation at 3000 rpm, 4 °C for 10 mins. The GM assay on serum, BALF and sputum will be performed with the Platelia *Aspergillus* enzyme immunoassay (Bio-Rad, California, USA) according to the manufacturer’s instructions. Tests for serum and BALF GM will be considered positive at cut-off values of ≥0.5 ODI and ≥ 1.0 ODI, respectively.

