### *A*-DNA extraction and RT-PCR

Fungal DNA will be extracted from 1.5 mL of the sputum suspension with the commercial MycXtra fungal DNA extraction kit (Myconostica Limited, Manchester, UK), and *A*-DNA will be detected with the MycAssay *Aspergillus* kit (Myconostica Limited, Manchester, UK), according to the manufacturer’s instructions. PCR runs will be performed on a CFX Connect™ RT-PCR system (Bio-Rad, California, USA) by targeting a portion of the 18S ribosomal gene, in accordance with the detection kit protocol. Ten microliters of extracted DNA will be used in a final reaction volume of 25 μL. The PCR protocol is as follows: 10 mins at 94 °C; 10 s at 94 °C, 58 s at 57 °C, and 20 s at 72 °C for 40 cycles. The cycling threshold will be recorded and used for subsequent analysis, including the determination of an optimal cut-off value, based on which the sputum samples will be regarded as positive or negative for *Aspergillus* infection.

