### Statistical analysis

The data will be analysed with SPSS 22.0 software (IBM Corp, Armonk, NY, USA). Two analyses will be performed based on the IPA classification, one in which patients with possible IPA will be excluded in the calculation and a second analysis in which patients with possible IPA will be classified as not having IPA. Therefore, the comparisons and analyses will be (1) proven/probable IPA versus no IPA, and (2) proven/probable IPA versus possible/no IPA [43]. The sensitivity, specificity, negative predictive value (NPV), positive predictive value (PPV), and diagnostic odds ratio, including 95% confidence intervals, will be calculated for different biomarkers. ROC analysis will be performed and AUC (including 95% CI) and cut-off values will be established from the ROC curves for GM, RT-PCR, TAFC and bmGT. The McNemar χ^2^ test will be used to compare sensitivity, specificity, NPV, and PPV between different assays. The difference in hospital stay and the survival between possible or no IPA versus proven or probable IPA will be analysed with chi-square tests, and the relationships between the levels of biomarkers and the hospital stay and survival will be analysed via regression models. *P* < 0.05 will be defined as statistically significant.

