This study has some limitations that should be considered. The categories of probable and possible IPA are proposed for immunocompromised patients only in the consensus report by the EORTC/MSG. However, this report recognizes that the revised definition of IPA does not necessarily apply to immunocompetent patients as it is difficult to find a sufficient basis for identifying appropriate host factors. Patients with URD may possess much different risk factors to *Aspergillus* infection compared to those immunocompromised individuals. As in the study by Prattes et al. [11], pre-existing respiratory disease is added as an independent host factor to establish the diagnosis in our study. We will also conduct post hoc analyses of the host factors linked to diagnosis and prognosis for further investigation. The concentration of biomarkers in the sputum may fluctuate with the production and expectoration of the sputum and the releasing of the biomarkers from the infection site. However, this study already includes a great number of biomarkers from different sample types with a comparable large sample size, and we do not perform serial tests for sputum biomarkers at different time points across the disease course, which may lead to the underestimation of the diagnostic performance of several biomarkers. Further study may be warranted to investigate the dynamic variation of different *Aspergillus* biomarkers in sputum.

In conclusion, the design and protocol of a clinical trial that investigates the performance of sputum signatures for the diagnosis and prognosis of IPA in patients with URD are presented here. The results of this innovative study are expected to provide answers to the following questions. Are sputum signatures valuable diagnostic tools for IPA in patients with URD? Which signature is the strongest potential candidate? Would the modified host factors be appropriate for this patient population? What disease course of IPA would present in this population? The study findings will provide evidence and novel insights into these areas, which have not been accessed.

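### Sputum cut-offs are taken from the study's own ROC curves and then evaluated and compared by McNemar in the same patients: accuracy is moderately overstated, and the tests cannot rank the markers

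*Protocol article*

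**What the plan says.** All references are to the protocol article.

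- **Source of the cut-offs.** Statistical analysis: "cut-off values will be established from the ROC curves for GM, RT-PCR, TAFC and bmGT". The rule for picking the point on the curve is not named.
- **Use of the cut-offs.** The section on A-DNA extraction and RT-PCR describes the "determination of an optimal cut-off value, based on which the sputum samples will be regarded as positive or negative". The threshold found in the study is therefore the one used to classify the study's own samples.
- **What is reported.** Sensitivity, specificity, NPV, PPV "and diagnostic odds ratio, including 95% confidence intervals, will be calculated for different biomarkers".
- **How assays are compared.** The McNemar chi-square "test will be used to compare sensitivity, specificity, NPV, and PPV between different assays", with P "< 0.05 will be defined as statistically significant". AUCs are to be estimated with 95% confidence intervals, but no test between AUCs is described.
- **Assays that are not tuned.** GM detection: "Tests for serum and BALF GM will be considered positive at cut-off values of" 0.5 and 1.0 ODI or above, respectively. The lateral flow device (LFD) is read as test line present or absent.
- **Cohort.** Sample size calculation: one cohort of at least 118, made up of 59 cases and 59 controls. No separate validation group is described.
- **The question to be answered.** The Discussion asks: "Which signature is the strongest potential candidate".

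**The concern.** A cut-off chosen because it separates these cases from these controls will look better in these patients than in new ones. Accuracy reported at that cut-off is optimistic, and an interval that treats it as fixed ignores the uncertainty of the choice. Tuned markers (sputum GM, RT-PCR, TAFC, bmGT) gain from this; LFD does not.

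The comparison has a second problem. Two markers with the same ROC curve will usually be cut at different points on it, because each cut-off is a noisy estimate. Their sensitivities and specificities then differ although neither marker discriminates better. McNemar is the only between-assay test that the article names, so it would carry the answer to the Discussion's question about the strongest signature. The Discussion also relies on these cut-offs to separate colonization from infection, so optimistic figures could reach practice.

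**Working it through.** **1. The plan's own figure.** The article gives n = z²·V/d², with V = 0.0099·exp(−a²/2)·(6a² + 16) and a = 1.414·Φ⁻¹(AUC).

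- Φ⁻¹(0.795) = 0.824, so a = 1.165 and a² = 1.357.
- V = 0.0099 × 0.507 × 24.14 = 0.1213.
- n = 3.8415 × 0.1213 / 0.09² = 57.5, rounded up to 58 per group against 59 stated.

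The planned size is reproduced within rounding. It concerns the AUC only, so cut-off selection does not touch it.

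**2. Simulation set-up.** From the article: 59 cases, 59 controls, AUC 0.795, 5% level. Assumed, because the article gives no figure: binormal equal-variance markers, within-group correlation between markers of 0 to 0.9, and the maximum Youden index as the main cut-off rule. Each setting used 2,000 to 3,000 simulated trials. The two markers have identical true ROC curves.

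**3. Optimism at the chosen cut-off (Youden rule).**

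| | Apparent, same patients | True, at that cut-off | Difference |
|---|---|---|---|
| Sensitivity | 0.762 | 0.720 | 0.042 |
| Specificity | 0.734 | 0.702 | 0.032 |
| Youden index | 0.496 | 0.422 | 0.074 |

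The Youden index is overstated by about 0.06 at AUC 0.90 and about 0.08 at AUC 0.70.

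**4. McNemar between two markers with identical ROC curves.** The figures are the percentage of trials with P < 0.05 for sensitivity or specificity.

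| Correlation | Both tuned: exact | Both tuned: uncorrected χ² | Both fixed: exact | Both fixed: uncorrected χ² |
|---|---|---|---|---|
| 0 | 33.8 | 42.0 | 5.7 | 10.2 |
| 0.3 | 38.4 | 45.4 | 5.6 | 9.4 |
| 0.6 | 43.9 | 50.7 | 4.6 | 8.4 |
| 0.9 | 43.7 | 53.0 | 3.4 | 9.1 |

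Continuity-corrected results lie close to the exact ones. The headline ranges of 33–39% and 41–46% correspond to low correlation (about 0 to 0.3); stronger correlation gives higher rates. The 9–10% with fixed cut-offs reflects two tests at 5% each: 1 − 0.95² = 9.75%.

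One tuned marker against a fixed-threshold test of LFD type (correlation 0.3) gives about 24% for sensitivity and for specificity separately (uncorrected).

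**5. Dependence on the cut-off rule** (correlation 0.3 and 0.6, uncorrected χ²).

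- Closest to the top-left corner: 10–13% per measure, 18–22% for either.
- Specificity of at least 0.90: 26–27% for sensitivity. Optimism is only about 1 point each (sensitivity 0.443 against 0.430, specificity 0.915 against 0.905).

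**6. A test that needs no cut-off.** A paired DeLong comparison of the two AUCs rejects in 4.6–5.2% of trials, close to nominal.

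**The case against.** **The rejections are not ordinary false positives.** McNemar tests equal sensitivity (or specificity) at the cut-offs in use. When two tuned cut-offs fall at different points on one curve, those quantities really do differ. Among simulated trials with any rejection, 94–97% showed sensitivity and specificity moving in opposite directions, a trade-off that the reader can see. A reader might infer from the table that the plan will often crown one of two equal markers as better overall. That does not follow: rejections without a visible trade-off occurred in only about 1–3% of trials. Between two tuned markers the optimism also largely cancels. This part stands. What remains is that the tests do not answer the ranking question.

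**The direction against serum and BALF GM is not known.** A reader might infer that tuning favours sputum markers over these fixed-threshold tests. But Table 2 makes a positive serum or BALF GM part of the mycological criteria, hence of probable IPA, which favours serum and BALF GM. The net direction cannot be read from the document. The argument holds only for LFD.

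**The optimism is modest.** With 59 per group, a binomial 95% interval around 0.76 is about ±1.96·√(0.76 × 0.24/59) = ±0.11, wider than the 3 to 4 point bias. This is true, but the bias is systematic and the interval does not show it.

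**This is a condensed article.** The cut-off rule and any internal validation may stand in a fuller document, so their absence here is not itself the fault. The article does, however, positively fix the source of the thresholds, their use in the same samples, the test and the level. That combination can be judged as written.

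**Conclusion.** The point holds in a limited form and should be fixed. Followed as written, the plan gives sensitivity and specificity that are each about 3 to 4 points too high (Youden index by about 0.07) for the four tuned sputum markers, which favours them over LFD. It also provides between-assay tests that often reject for markers of equal discrimination: about 33–39% (exact or corrected) or 41–46% (uncorrected) for either measure, against about 5% or 9–10% with fixed cut-offs.

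These sizes assume a Youden rule, binormal markers, AUC 0.795, 59 per group and low between-marker correlation. Other rules give smaller figures, but every rule tried showed some optimism and raised rejection rates. The rejections mostly reflect different positions on the same curve, so they are uninformative about which signature is strongest. They are not evidence that an inferior marker would be selected.

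The AUC estimates, their role as the overall accuracy index and the sample size are not affected.

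**What to change.** 1. Rank sputum GM, RT-PCR, TAFC and bmGT by a paired comparison of AUCs (DeLong) in the same patients. The study is already sized on the AUC.
2. Name the rule that selects each cut-off. Report sensitivity, specificity, PPV, NPV and diagnostic odds ratio at ROC-derived cut-offs with bootstrap optimism correction, and with intervals that repeat the cut-off selection in every resample.
3. Label McNemar p-values that involve a data-derived cut-off as exploratory, or replace them with bootstrap comparisons that repeat the selection. State which McNemar variant is used.

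No extra patients, samples or assays are needed. The cost is some additional analysis work, possibly outside the named SPSS 22.0 software, and slightly less favourable reported accuracy.

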**Methods:**

This is a prospective diagnostic trial. At least 118 participants will be recruited from respiratory wards and intensive care units. IPA is defined according to the EORTC/MSG criteria modified for patients with URD. Induced sputum and blood will be collected, and BALF will be obtained by bronchoscopy. Sputum biomarkers, including galactomannan, *Aspergillus* DNA, triacetylfusarinine and bis(methylthio)gliotoxin will be determined, and the presence of a JF5 antigen will be examined with a lateral fluid device. The sensitivity, specificity, negative predictive value, positive predictive value and diagnostic odds ratio will be computed for different biomarkers and compared using the McNemar χ^2^ test. Receiver operating characteristic analyses will be performed, and the cut-off values will be established. Participants will receive follow-up evaluations at 3 months and 6 months after recruitment. The difference in hospital stay and survival will be analysed, and the relationships between the levels of biomarkers and hospital stay and survival will be analysed via regression models.

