### Sputum induction and sample processing

Sputum induction using hypertonic saline (4.5%) and spirometry (KoKo PD Instrumentation, Louisville, KY) will be performed as previously described [38]. 4.5% saline will be inhaled from an ultrasonic nebulizer for doubling time periods (from 30 s to 4 mins), and a fixed cumulative sputum induction time of 15 min will be used for all participants.

Fungal culture will be performed on 100 μL of sputum plugs carefully separated from saliva and inoculated directly onto potato dextrose agar [39]. The plates will be sealed and incubated for 7 days at 37 °C. After 7 days, *Aspergillus* will be identified based on macroscopic and microscopic features.

A minimum volume of 0.5 mL of sputum plugs will be pipetted into a sterile falcon centrifuge tube, and 8 volumes of phosphate buffer solution will be added, vortexed and incubated at room temperature for 30 mins, and 1.5 mL of the above sputum suspension will be stored for *A*-DNA extraction and RT-PCR assay.

A total of 200 μL of filtered suspension will be used for quality assessment as previously described [38]. Briefly, in an adequate number of cells, the presence of pulmonary macrophages and the proportion of squamous cells are examined. A total cell count of leukocytes and cell viability is performed, and samples with a squamous cell percentage greater than 50% or viability less than 40% are excluded. The remainder of the sample will go through a sterile filter (Merk Millipore Ltd., Ireland) and will be stored in aliquots at − 80 °C for subsequent GM, LFD, TAFC and bmGT detection.

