### Sample size calculation

GM is the most studied biomarker for the diagnosis of IPA among our candidate signatures; therefore, the sample size calculation is based on the diagnostic accuracy of the sputum GM assay reported by previous studies. Receiver operating characteristics (ROC) curves show the trade-off between sensitivity and specificity, and the area under the curve (AUC) is considered as an overall index of accuracy for quantitative biomarkers. The sample size estimation is based on AUC reported previously [27].

With 95% confidence (*α* = 0.05) to guarantee the marginal error of estimate (i.e. the difference between true AUC and its estimate) does not exceed from a pre-determined value of d = 0.09, and expecting an equal number of diseased and non-diseased cases, the required sample size for each group is:1$$ \mathrm{n}=\frac{{\mathrm{z}}_{\frac{\alpha }{2}}^2\ \mathrm{V}\left(\hat{\mathrm{AUC}}\right)}{d^2} $$

V($$ \widehat{\mathrm{AUC}} $$) denotes the variance of $$ \widehat{\mathrm{AUC}} $$ that is estimated parametrically based on binormal assumption [41, 42]. This binormal assumption is chosen because our study implements a four-category rating scheme (i.e. proven IPA, probable IPA, possible IPA and no IPA). $$ \mathrm{V}\left(\widehat{\mathrm{AUC}}\right) $$ is calculated as follows:2$$ \mathrm{V}\left(\widehat{\mathrm{AUC}}\right)=\left(0.0099\times {e}^{\raisebox{1ex}{$-{a}^2$}\!\left/ \!\raisebox{-1ex}{$2$}\right.}\right)\times \left(6{a}^2+16\right) $$

where a = *φ*^−1^(AUC) × 1.414 and *φ*^−1^ is the inverse of standard cumulative normal distribution. With a pre-specified AUC of 0.795 according to Kimura et al. [27], the required sample size for each group is 59 after above calculation. Therefore, we will recruit a minimum number of 118 participants with 59 controls (no IPA) and 59 cases (proven or probable IPA).

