There are concerns about the specificity of the sputum assay related to colonization or contamination. Nevertheless, the four biomarkers (GM, JF5 antigen, TAFC, bmGT) in our study are produced and released during fungal growth. It is less likely that the increase in the levels of these biomarkers is a result of contamination of fungal spores. In addition, lower airway secretions will be used by sputum induction, and sputum quality control by squamous cell counting and viability calculation will further exclude the possibility of contamination. We will also determine an appropriate cut-off value of different sputum biomarkers, which will help to differentiate colonization from infection.

There are several highlights of this study. We systematically evaluate the validity of various biomarkers based on sputum from lower airways for the diagnosis of IPA for the first time; in particular, the establishment of a method that simultaneously detects TAFC and bmGT in sputum is first described and applied for patents and reported. Furthermore, the study population, i.e., patients with URD, has been increasingly recognized to present with IPA, which is associated with high mortality [12], but only has been addressed in a small number of studies. We assess the sputum biomarkers for IPA diagnosis in this population for the first time, and the results may help to provide novel, non-invasive and valuable diagnostic tools for IPA in patients with URD. In addition to sputum, serum and BALF will also be collected and compared for their diagnostic performance. In the statistical analysis, we will conduct two different analyses to investigate the impact of the possible IPA group on the interpretation of the results. Except for the investigation of diagnostic efficacy, we will also conduct a clinical follow-up to observe the prognosis of different types of IPA and further investigate host factors predisposing to IPA in patients with URD.

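### McNemar's test is prescribed for comparing PPV and NPV between assays, but it does not test equality of predictive values

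*Protocol article*

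**What the plan says.** The Statistical analysis section names one test for all between-assay comparisons of accuracy: the McNemar "test will be used to compare sensitivity, specificity, NPV, and PPV between different assays". The abstract says the accuracy measures "will be computed for different biomarkers and compared using the McNemar" test, and its list also includes the diagnostic odds ratio. The significance criterion is P "< 0.05 will be defined as statistically significant". No other method for comparing predictive values appears in the article.

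The assays are run on the same patients. Under Sputum induction and sample processing, aliquots of one processed sample are stored "for subsequent GM, LFD, TAFC and bmGT detection". The Discussion adds that "serum and BALF will also be collected and compared for their diagnostic performance". The Sample size calculation plans 59 cases (proven or probable IPA) and 59 controls (no IPA).

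**The concern.** McNemar's test compares two proportions measured on one common set of patients. Sensitivity meets that condition because every case is tested by both assays, and specificity meets it because every control is. Pairing of patients does not carry over to predictive values. The PPV of assay A is taken over the patients positive on A, and the PPV of assay B over those positive on B. These sets differ in size and overlap only in part. NPV has the same difficulty among the negatives.

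Whichever two-by-two table is fed to McNemar, the hypothesis tested is therefore something other than equal PPV or equal NPV. Two of the four measures named in the sentence would carry P values that answer another question. The protocol's conclusion asks which signature is the strongest candidate, and these P values could feed into that answer.

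**Working it through.** **The plan's own figure.** The sample size rests on AUC precision: "With 95% confidence", a margin that "does not exceed from a pre-determined value of d = 0.09", and "With a pre-specified AUC of 0.795". With the article's formulas:
- a = 1.414 × Φ⁻¹(0.795) = 1.165
- V = 0.0099 × exp(−a²/2) × (6a² + 16) = 0.1213
- n = 1.96² × 0.1213 / 0.09² = 57.5, so 58 per group against 59 stated

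The difference of one patient per group has no bearing here. The calculation does not involve PPV or NPV. I use the stated 59 and 59 below.

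**What McNemar tests.** Let b be the number positive on A only and c the number positive on B only. The statistic is (b − c)²/(b + c). Over all patients, b = c means equal numbers of positives. Within cases, it means equal sensitivity. Within controls, it means equal specificity. None of these is equality of PPV or NPV.

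**Two worked tables.** The cell counts are assumptions, since the article gives no paired tables. No continuity correction is used here.

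*Table 1, equal PPV.* A has 48 true and 16 false positives; B has 30 and 10. Both PPVs are 0.75 (48/64 and 30/40), and 36 patients are positive on both. Discordant cases are 20 and 2; discordant controls are 8 and 2.
- McNemar on all patients: (28 − 4)²/32 = 18.0, p = 0.00002
- McNemar within cases: (20 − 2)²/22 = 14.7, p = 0.0001
- Weighted generalised score test for paired PPV: statistic 0, p = 1.00

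*Table 2, unequal PPV and NPV, equal positivity.* A has 50 true and 10 false positives; B has 40 and 20. PPV is 50/60 = 0.83 against 40/60 = 0.67. NPV is 49/58 = 0.84 against 39/58 = 0.67. Discordant cases are 12 and 2; discordant controls are 2 and 12.
- McNemar on all patients: (14 − 14)²/28 = 0, p = 1.00
- McNemar within cases: (12 − 2)²/14 = 7.1, p = 0.008
- Weighted generalised score test: p = 0.0007 for PPV and p = 0.0008 for NPV

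**How often it goes wrong when PPVs are equal.** These are simulated trials with 59 cases and 59 controls, assays conditionally independent given disease status, continuity-corrected McNemar and nominal 5%. Assay A has sensitivity 0.90 and specificity 0.80. With equal group sizes, PPV = 0.90/(0.90 + 0.20) = 0.818. Assay B's specificity is set to give the same PPV, so 1 − specificity = sensitivity × 0.20/0.90.

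| Assay B sensitivity / specificity | McNemar on true positives | McNemar on overall positivity |
|---|---|---|
| 0.675 / 0.850 | about 80% | about 71% |
| 0.75 / 0.833 | 46% | 38% |
| 0.80 / 0.822 | 22% | 18% |
| 0.85 / 0.811 | 7% | 7% |

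The weighted generalised score test for paired PPV rejects in about 5% of trials in all four rows.

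**How often it misses a real difference.** With the margins of Table 2 and conditional independence, McNemar on overall positivity rejects in about 3% of trials. McNemar on true positives rejects in about 48%.

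**The case against.** The strongest reply concerns importance. The sample size is built on the AUC of sputum galactomannan. Whether sputum signatures are useful, and which is best, can be judged from AUC with confidence intervals and from sensitivity and specificity, for which McNemar is correct. PPV and NPV will also be reported with 95% confidence intervals, and the choice of test does not change those. All of this stands and limits the damage to the PPV and NPV P values.

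A second reply is that the error depends on unknown accuracies. This also stands. The article gives no expected sensitivity or specificity for these assays in this population and no between-assay correlation. Conditional independence is unlikely to hold exactly for assays run on aliquots of one sputum sample. When the two assays have the same sensitivity and specificity (0.80 and 0.80), McNemar rejects in only about 3% of trials.

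Three stronger readings are therefore not supported:
- A reader might infer that assays with equal PPV will be declared different. They can be, and the chance ranges from about 7% to 80% in the cases above.
- A reader might infer that assays with different PPV but equal positivity will always be declared equal. That follows only if McNemar is run on overall positivity, and the article does not say which table would be used.
- A reader might infer that half of the comparative analysis is lost. Two of four named measures are affected, but they are not half of the study's evidence.

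What the objections do not touch is the mismatch itself. The article names the test for PPV and NPV, so this is a wrong specification and not a detail left to an analysis plan.

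**Conclusion.** The point holds for PPV and NPV only. As written, their comparison tests equal positivity, or equal sensitivity or specificity, instead of equal predictive values, and the resulting P values can mislead in either direction. That conclusion follows from the definitions and needs no assumed figures. The size of the error does rest on assumptions: the accuracies, conditional independence and the 59:59 split. Under them, false rejection at a common PPV of 0.818 grows with the gap in sensitivity, from near nominal when the gap is 0.05 to about 80% or 71%, depending on the table used, when it is 0.225. McNemar for sensitivity and specificity is right and should stay. The predictive-value estimates and their intervals, the ROC analysis and the recruitment target need no change.

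**What to change.** In the Statistical analysis section, restrict McNemar to two comparisons: sensitivity within proven/probable IPA, and specificity within the non-IPA group of each analysis (no IPA in the first, possible/no IPA in the second). For PPV and NPV, name one method for paired predictive values:
- a generalised or weighted generalised score test
- GEE marginal regression
- relative PPV and NPV with confidence intervals from a bootstrap that resamples patients

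Confirm that the chosen method can be run in SPSS 22.0, the only software the article names, or name another tool. Align the abstract, whose sentence currently extends McNemar to every measure it lists. The cost is a sentence or two and a little extra programming. No new data are needed, and the change should be made before the analysis.

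### McNemar at P < 0.05 ignores that the cut-offs of four sputum markers are chosen from ROC curves in the same patients, so comparisons involving them generally do not hold the 5% level

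*Protocol article*

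**What the plan says.** The Statistical analysis section of the protocol article states that "cut-off values will be established from the ROC curves for GM, RT-PCR, TAFC and bmGT". It then says that the McNemar χ² "test will be used to compare sensitivity, specificity, NPV, and PPV between different assays", and closes by stating that P "< 0.05 will be defined as statistically significant".

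Two other places confirm that these cut-offs come from the study data. The section on A-DNA extraction and RT-PCR records the cycling threshold for later analysis, "including the determination of an optimal cut-off value, based on which the sputum samples will be regarded as positive or negative". The Discussion says: "We will also determine an appropriate cut-off value of different sputum biomarkers".

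Other assays have fixed rules. Serum and BALF GM are positive from 0.5 and 1.0 ODI (GM detection). The LFD is read as test line present or absent (LFD performance).

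The article describes no second sample, sample split or resampling to allow for the choice of cut-off. Among the questions that the study is to answer, the Discussion lists "Which signature is the strongest potential candidate".

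**The concern.** McNemar's test counts the patients in whom two assays disagree and asks whether the disagreements split evenly. Its 5% level assumes that what counts as positive was settled before the data were seen. Here each of four markers gets its own threshold from its own ROC curve, in the patients who then enter the test.

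Suppose two markers have the same ROC curve. Their chosen thresholds will still fall at different points along it by chance. One marker then shows higher sensitivity and lower specificity than the other, and McNemar reports this as a difference between assays. At stake is the reading of these p-values: an apparent sensitivity advantage may be only a lower threshold, paid for in specificity. The problem lies in a single test of a single pair, so it is separate from multiplicity and from power.

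**Working it through.** **Inputs from the protocol (Sample size calculation).** "With a pre-specified AUC of 0.795 according to" an earlier study of sputum GM; a margin of error that "does not exceed from a pre-determined value of d = 0.09"; 59 cases and 59 controls.

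**Assumptions.** Two equally accurate markers, normal with equal variance; between-marker correlation 0, 0.3, 0.5 or 0.7; a two-sided 5% test. The protocol gives no correlation and no rule for choosing a cut-off, so both were varied.

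**The plan's own figure.** The plan gives no error rate for McNemar. Its one computed figure is the sample size:
- a = 1.414 × Φ⁻¹(0.795) = 1.414 × 0.824 = 1.165
- V = 0.0099 × exp(−a²/2) × (6a² + 16) = 0.0099 × 0.507 × 24.14 = 0.1213
- n = 1.96² × 0.1213 / 0.09² = 57.5, so 58 per group against 59 stated. An AUC rounded to 0.79 gives 58.3, so 59. This agrees closely enough to use the plan's figures as they stand.

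**Rough check of the mechanism (correlation 0, Youden).**
- Separation of the groups: μ = √2 × 0.824 = 1.165. True sensitivity at the best cut-off: Φ(1.165/2) = Φ(0.583) = 0.72.
- Standard error of the sensitivity difference if cut-offs are fixed: √(2 × 0.72 × 0.28 / 59) = 0.083.
- In the simulation, the true sensitivity at the cut-off chosen from the data had a standard deviation of 0.10. For a difference of two markers this is √2 × 0.10 = 0.14, which is larger than the 0.083 that McNemar allows for.
- Treating the two sources as independent, the total is √(0.083² + 0.14²) = 0.164. The limit 1.96 × 0.083 = 0.162 is then 0.99 standard deviations, which gives a two-sided rate of about 32%. The simulation gives 30%.

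**Simulation, AUC 0.795, 59 + 59.** Share of null studies in which one sensitivity test is significant, over the four correlations:

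| Cut-off rule | Uncorrected χ² | Continuity-corrected or exact |
|---|---|---|
| Both fixed in advance | 4.5–5.9% | about 2.6–3.4% |
| Youden for both | 30, 33, 36, 37% (correlation 0, 0.3, 0.5, 0.7) | 23–32% |
| Each at its observed 90% specificity | 23–25% | not recorded |
| Closest-to-corner for both | 8–15% | 5–11% |
| Youden for one, fixed for the other | 23–34% | 18–28% |

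The Youden-for-both and 90%-specificity rows used 10,000 studies per setting, the others 2,500. At other AUCs the uncorrected Youden rate is 43–49% (AUC 0.70) and 18–26% (AUC 0.90). Closest-to-corner at AUC 0.90 gives 5–8%.

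**Effect of a detection floor.** TAFC and bmGT have a lower quantitation limit of 1.56 ng/mL (TAFC and bmGT detection) and were undetectable in all four unspiked pilot sputa (Results of pilot study). PCR runs for 40 cycles, so negative samples may have no threshold value. With Youden cut-offs, correlation 0.5, AUC 0.795 before flooring and 3,000 studies per setting, the uncorrected rate by assumed share of controls at the floor is:

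| None | 50% | 70% | 80% | 90% | 95% |
|---|---|---|---|---|---|
| 35% | 34% | 18% | 10% | 7% | 6% |

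Closest-to-corner with 70–95% at the floor gives 5–6%.

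**Alternatives under the same null.** The paired DeLong comparison of AUCs rejects in 4.3–5.0%. A bootstrap of the sensitivity difference at 80% specificity, with each cut-off re-derived in every resample, rejects in 4.3% of 600 studies (200 resamples each).

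**The case against.** The strongest objection is that the size depends on things the protocol leaves open. It names no cut-off rule, and an article may leave that to the full plan. The high rates come from Youden cut-offs on continuous markers without a floor. Of the four markers GM fits that description most readily, and a pair needs two. This stands: a reader might infer that any such test is falsely significant a third of the time, and the document does not support a flat figure.

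Three further limits also stand.
- A reader might infer that every comparison between assays is affected. Those among LFD, serum GM and BALF GM have fixed rules and are not.
- A reader might take a significant result to be pure noise. In 83–85% of the significant Youden studies the true sensitivities at the chosen cut-offs did differ by more than 10 points. The test often detects a real difference between thresholds; the mistake is to read it as a difference in marker accuracy.
- The plan also reports specificity, diagnostic odds ratio and AUC with confidence intervals. It does not say that McNemar p-values alone decide which signature is strongest. The sample size rests on AUC precision and is untouched.

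None of this rescues the stated method. The article itself fixes both the source of the cut-offs and the test, and McNemar makes no allowance for the first whichever rule is used. One optimised marker is enough for inflation, so sputum GM against LFD or BALF GM is exposed too. McNemar is also the only test that the article names for comparing assays.

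**Conclusion.** The analysis is wrong as written for comparisons that involve sputum GM, RT-PCR, TAFC or bmGT at a ROC-derived cut-off. There the McNemar p-values for sensitivity and specificity generally do not hold the 5% level as evidence that one marker is more accurate.

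The size is conditional. For two equally accurate continuous markers at AUC 0.795 and 59 + 59 it is roughly 25–37% per sensitivity test under Youden (23–37% over every form of the test and correlation tried) and about 5–15% under closest-to-corner. It comes near nominal when most controls share a floor value. That may be so for TAFC and bmGT, but four pilot samples only suggest it. Confidence is high in the mechanism and moderate in any single figure.

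**What to change.** For comparisons involving a ROC-derived cut-off, replace McNemar by one of:
- a paired AUC comparison (DeLong) between quantitative markers, which also matches the AUC basis of the sample size; or
- a comparison of sensitivities at one specificity fixed in advance, using a patient-level bootstrap stratified by case and control that re-derives each cut-off in every resample.

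Fixing the specificity while keeping McNemar is not enough, as the 23–25% row shows; the cut-off must be re-derived. The LFD is binary and cannot be moved to a chosen specificity. Against it, the quantitative marker could be cut at the LFD's observed specificity within each resample; this variant was not simulated.

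Keep McNemar only where both cut-offs are fixed in advance, and name the rule by which the reported cut-offs are chosen.

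The cost is a change of analysis wording and a short script outside the SPSS menus, with no new patients or assays. Fewer differences will be declared significant.
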